### Interventions

All interventions will take place at the JRH and McMaster site facilities. HIIT and MICT will consist of 12 weeks of training with three sessions per week performed on alternate days to avoid overtraining and maximize adaptations [50]. Initially, training was to be performed in a group training session on recumbent steppers with a 2:5 trainer-to-participation format, as group training may be an important facilitator for adherence to exercise in stroke [51]. However, to reduce the risk of COVID-19 infection, we  have been using a 1:1 trainer-to-participant format during training sessions. Recumbent steppers were chosen because they will; 1) allow participants with a wide range of functional abilities to exercise at high intensities [52]; 2) have been previously described as safe and effective for implementing HIIT [53] and MICT [54] training protocols in stroke populations and allow for exercise intensity to be controlled in an easier manner than using treadmill training; 3) reduce the risk of falls due to the seated position required during exercise; and 4) involve both upper and lower limbs, training muscles that are evaluated in TMS and motor function outcomes, facilitating an examination of relationships between upper and lower limb functions. Heart rate (HR), rate of perceived exertion (RPE), and, if needed, BP will be monitored continuously throughout each training session as individuals who take beta-blockers will exhibit a blunted HR response.

Exercise intensity will be determined using the HR reserve (HRR) method calculated as HRR = (max HR at peak VO_2_peak – resting HR) × (% exercise intensity) + (resting HR), in combination with RPE [55]. For participants taking HR limiting medication (e.g., beta-blockers), a modified HRR equation will be used (HRR = 0.8 × [max HR at peak VO_2_peak – resting HR] + [resting HR]) [56]. Both MICT and HIIT will involve 3-min warm-up and 2-min cool-down periods at 30% of HRR.

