#### HIIT

We will use an adjusted HIIT protocol that has been described previously in individuals with chronic stroke [57]. It will involve ten 60-s intervals of high-intensity bouts interspersed with nine 60-s low-intensity intervals [57] (Fig. 2). The high-intensity workload will initially start at 80% of HRR and will be increased by 10% every 4 weeks. Low-intensity bouts will be performed at 30% of HRR. To reduce sudden changes in BP and ensure that target intensity is achieved [58], the workload at the low-intensity interval will increase gradually over 15 s prior to the next high-intensity interval. The total duration of the HIIT session will be 24 min.

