#### MICT

We will use a conventional MICT protocol typically employed in stroke rehabilitation programs. Initial intensity will start at 40% HRR and will progressively be increased by 10% HRR every 4 weeks up to 60% HRR and time (5 min) until the end of the intervention (Fig. 2). If initial tolerance is low, to achieve 20 min of continuous exercise, the initial intensity will be set at <40% HRR. Intensity will be increased by 5–10% HRR and/or 5 min per week until 30 min of continuous exercise at 40% HRR are achieved. The total duration for the MICT session will be 35 min.

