### Adherence and modification to interventions

Adherence to training in both HIIT and MICT groups will be monitored by exercise trainers who will track attendance in training sessions and adherence to required training intensities as described in this protocol (see below), using the Borg scale and Polar HR devices. If participants miss sessions of training, they will be offered make-up sessions to complete the full 36 sessions of training. During the period between T1 and T2, study coordinators will contact participants by telephone to encourage participant retention at T2. These calls will also serve to assess activity level post-training (see below).

If participants desire to stop training and develop health conditions or injury that preclude safe participation of exercise over the course of the intervention, we will discontinue training. Participants will be asked to not participate in another structured exercise regimen or intervention over the course of their participation in either the HIIT or MICT group; otherwise, they will not be allowed to continue participation. However, during the period between T1 and T2, participants will not be asked to refrain from further participation in exercise. This may influence outcomes at assessments at T2, as participants may engage in another exercise program after completing T1 assessments. In order to address this, we will use the Physical Activity Scale for Individuals with Physical Disabilities (PASIPD) [59] and administer it midway in between T1 and T2.

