##### Secondary outcome — cardiorespiratory fitness

Cardiorespiratory fitness will be assessed by assessing the VO_2_peak of participants. VO_2_peak will be determined by a graded cardiopulmonary exercise test (CPET) on a recumbent stepper which has been validated for individuals with stroke [54] and has been used by our lab in a previous study [22]. Cardiovascular responses will be monitored using a 12-lead ECG and BP monitor. RPE will be recorded during the exercise test [75].  Each site will have a medical support team, including an on-call physician, in the case of any medical emergency during this assessment.

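### The heart-rate equation for participants on HR-limiting medication has no intensity term, so as printed it sets 80% of reserve in both arms, in every week and phase

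*Protocol article*

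**What the plan says.** All references are to the protocol article.

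- **Interventions, standard equation:** "HRR = (max HR at peak VO_2_peak – resting HR) × (% exercise intensity) + (resting HR), in combination with RPE". The percentage is the only term that can carry arm, week and phase.
- **Interventions, participants on HR-limiting medication such as beta-blockers:** "a modified HRR equation will be used (HRR = 0.8 × [max HR at peak VO_2_peak – resting HR] + [resting HR"]). The rule is not limited to one arm, to the high-intensity bouts or to particular weeks.
- **Interventions, warm-up and cool-down:** "Both MICT and HIIT will involve 3-min warm-up and 2-min cool-down periods at 30% of HRR".
- **HIIT:** "The high-intensity workload will initially start at 80% of HRR and will be increased by 10% every 4 weeks", and "Low-intensity bouts will be performed at 30% of HRR".
- **MICT:** the start is 40% of reserve, to "progressively be increased by 10% HRR every 4 weeks up to 60% HRR".
- **Adherence and modification to interventions:** trainers track "adherence to required training intensities as described in this protocol (see below), using the Borg scale and Polar HR devices".
- **Discussion:** medication is to be taken into account so that the prescribed intensity fits the participant's group, and the heart-rate and workload data will be used to see whether participants reach what was prescribed.

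**The concern.** Exercise intensity is the factor that this trial randomises. The equation printed for medicated participants returns one fixed heart rate, so it cannot express the difference between HIIT and MICT, the four-weekly progression, or the alternation of hard and easy intervals that defines HIIT.

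Two things are at stake:

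- **Delivery.** If trainers followed the printed line, medicated MICT participants would train at the HIIT starting intensity and medicated HIIT participants would have no low-intensity intervals. The arms would not differ in target intensity for these participants. An 80% target for people on such medication in the moderate arm would also be a safety matter.
- **Assessment of adherence.** Even if trainers did something sensible, the protocol's reference for adherence and attainment is wrong for these participants.

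**Working it through.** **Inputs.** The two equations and the 30% phases come from Interventions; the HIIT and MICT steps come from the sections of those names. One assumption is needed: the HIIT increase of 10% is read as percentage points, giving 80/90/100% over 12 weeks. The relative reading is shown in step 5.

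**Step 1. What intensity does the printed equation imply?** Set the two equations equal, with p the intensity, max the tested peak heart rate and rest the resting heart rate:

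p × (max − rest) + rest = 0.8 × (max − rest) + rest

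This gives p = 0.80 for any peak and resting heart rate.

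**Step 2. Compare with the stated programme.** Values are percentages of measured reserve. The scaled column assumes that 0.8 was meant to multiply the reserve before the percentage is applied: 0.8 × p.

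| Phase | Standard equation | As printed | 0.8 as scaling factor |
|---|---|---|---|
| Warm-up, cool-down, low bouts | 30 | 80 | 24 |
| MICT, three steps | 40 / 50 / 60 | 80 / 80 / 80 | 32 / 40 / 48 |
| HIIT high bouts, three steps | 80 / 90 / 100 | 80 / 80 / 80 | 64 / 72 / 80 |
| HIIT minus MICT | 40 / 40 / 40 | 0 / 0 / 0 | 32 / 32 / 32 |

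- Printed minus standard: 80 − 30 = 50 points in the low phases; 80 − 40 = 40, 80 − 50 = 30 and 80 − 60 = 20 points in MICT; 0, −10 and −20 points in the HIIT bouts.
- Printed minus scaled: 80 − 24 = 56 points in the low phases; 48, 40 and 32 points in MICT; 16, 8 and 0 points in the HIIT bouts.
- So the printed value is wrong at every MICT step under either reading. It matches one HIIT step only: the first under the standard equation, the last under scaling.

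**Step 3. Share of a HIIT session affected by the 30% conflict.** The session is 3 + 10 + 9 + 2 = 24 min. Time at 30% is 3 + 9 + 2 = 14 min, and 14/24 = 58% (ignoring the 15-s ramps).

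**Step 4. Distance between the two corrections.** Standard minus scaled is 16/18/20 points in HIIT and 8/10/12 points in MICT. If the reserve is scaled for the training steps but the warm-up stays at 30% of unscaled reserve, the warm-up lies only 32 − 30 = 2 points below the first MICT step.

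**Step 5. Relative reading of the HIIT increase.** 80, 80 × 1.1 = 88, 88 × 1.1 = 96.8. The standard contrast is then 40, 88 − 50 = 38 and 96.8 − 60 = 36.8. The printed contrast is still 0.

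**Step 6. In beats per minute.** The document gives no heart rates, so these are assumed. With rest 65 and peak 120, reserve is 55:

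| Phase | Standard | As printed | Scaled |
|---|---|---|---|
| 30% phases | 81.5 | 109 | 78.2 |
| MICT steps | 87.0 / 92.5 / 98.0 | 109 | 82.6 / 87.0 / 91.4 |
| HIIT steps | 109.0 / 114.5 / 120.0 | 109 | 100.2 / 104.6 / 109.0 |

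For rest/peak pairs from 60/110 to 70/140, the printed target exceeds the standard one by 25 to 35 beats/min in the 30% phases and by 20 to 28 beats/min at the first MICT step.

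**Step 7. Could the percentage be applied to the printed result?** With rest 65 and peak 120, 30% of 109 is 32.7 beats/min, below resting heart rate. The same happens for the other two pairs (30.0 against rest 60; 37.8 against rest 70). That reading fails.

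**The case against.** The strongest reply is that nobody intended a flat 80%. The sentence after the equation sets 30% for both arms, the HIIT and MICT sections give arm-specific percentages without exempting medicated participants, and the Discussion says that medication is considered so that intensity fits the group. On this view the printed expression is a lowered ceiling, and the percentages apply to the reserve below it. The source cited for the equation, the protocol figure (not shown) and the sites' operating procedures may settle the matter. Perceived exertion is used alongside heart rate, and supervision is one to one.

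Much of this stands. A dropped term is the likeliest explanation, and no misdelivered dose is claimed. But the ceiling reading gives p × 0.8 × (max − rest) + rest, which is the scaled version above and needs the very term the printed equation lacks. The context shows that a flat 80% was not meant; it does not show which of two different prescriptions was. Perceived exertion may soften the practical effect but does not correct the equation. Training across sites, described in the Discussion, may have settled one working version, but the document does not show which.

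It is also fair that using the standard equation for everyone would depart from a cited method that cannot be consulted here. That is why the fix leaves the choice to the investigators.

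**Conclusion.** The concern holds. As printed, the equation gives exactly 80% of reserve for every medicated participant, in both arms and at all times. It exceeds the MICT steps by 40/30/20 points and the 30% phases by 50 points, measured against the standard equation, and reduces the contrast between arms from 40 points to 0. The p = 0.80 result is algebra and depends on no assumed heart rates. The 80/90/100% HIIT steps are an assumption, and the relative reading does not change the conclusion.

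This is an error in the printed dosing rule for the factor under test, not a detail left to a fuller document. Its effect on the trial result cannot be computed: the document gives neither the share of participants on HR-limiting medication nor what the sites delivered. It should be corrected, but there is no basis for claiming bias or a loss of power.

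**What to change.** Correct the equation so that the arm- and week-specific percentage enters it, and state which version applies:

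- **(a) If 0.8 is a scaling factor:** target HR = 0.8 × (max HR − resting HR) × (% exercise intensity) + resting HR. Say that the low phases are scaled too (24% of measured reserve).
- **(b) If it is not:** use the standard equation for everyone. The argument for this is that peak heart rate already comes from the participant's own test; under cardiorespiratory fitness, "VO_2_peak will be determined by a graded cardiopulmonary exercise test (CPET) on a recumbent stepper".

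Apply the same version at both sites, brief the trainers, and check the training logs to see which version was used. If the printed one was used, report delivered intensity by arm among medicated participants. Any sensitivity analysis is optional; if one is done, define the subset by HR-limiting medication at baseline, not by the intensity delivered, so that the randomised comparison is kept.

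The cost is one corrected line, a briefing and a log check. Heart rate is tracked in training, and medication use is recorded at all time points (Assessments). The drawback is that, if practice changes, medicated participants trained before and after the correction may have had different doses, which would have to be reported.

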#### HIIT

We will use an adjusted HIIT protocol that has been described previously in individuals with chronic stroke [57]. It will involve ten 60-s intervals of high-intensity bouts interspersed with nine 60-s low-intensity intervals [57] (Fig. 2). The high-intensity workload will initially start at 80% of HRR and will be increased by 10% every 4 weeks. Low-intensity bouts will be performed at 30% of HRR. To reduce sudden changes in BP and ensure that target intensity is achieved [58], the workload at the low-intensity interval will increase gradually over 15 s prior to the next high-intensity interval. The total duration of the HIIT session will be 24 min.

**Fig. 2 Fig2:**
[figure not shown]
MICT and HIIT protocol

#### MICT

We will use a conventional MICT protocol typically employed in stroke rehabilitation programs. Initial intensity will start at 40% HRR and will progressively be increased by 10% HRR every 4 weeks up to 60% HRR and time (5 min) until the end of the intervention (Fig. 2). If initial tolerance is low, to achieve 20 min of continuous exercise, the initial intensity will be set at <40% HRR. Intensity will be increased by 5–10% HRR and/or 5 min per week until 30 min of continuous exercise at 40% HRR are achieved. The total duration for the MICT session will be 35 min.

### Adherence and modification to interventions

Adherence to training in both HIIT and MICT groups will be monitored by exercise trainers who will track attendance in training sessions and adherence to required training intensities as described in this protocol (see below), using the Borg scale and Polar HR devices. If participants miss sessions of training, they will be offered make-up sessions to complete the full 36 sessions of training. During the period between T1 and T2, study coordinators will contact participants by telephone to encourage participant retention at T2. These calls will also serve to assess activity level post-training (see below).

If participants desire to stop training and develop health conditions or injury that preclude safe participation of exercise over the course of the intervention, we will discontinue training. Participants will be asked to not participate in another structured exercise regimen or intervention over the course of their participation in either the HIIT or MICT group; otherwise, they will not be allowed to continue participation. However, during the period between T1 and T2, participants will not be asked to refrain from further participation in exercise. This may influence outcomes at assessments at T2, as participants may engage in another exercise program after completing T1 assessments. In order to address this, we will use the Physical Activity Scale for Individuals with Physical Disabilities (PASIPD) [59] and administer it midway in between T1 and T2.

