### Statistical analysis

Estimates of the effect of HIIT and MICT at the end of the intervention (T1) for all outcomes will be determined using linear mixed models. Baseline scores (at T0), age, and sex will be included as covariates for sub-analysis. The primary analysis focuses on T1, but T2 will also be included in the model (except for enjoyment, which will not be measured at T2) to increase the statistical efficiency of the estimate. If group interaction effects are significant, *t*-tests based on the linear mixed models will be employed as planned pairwise comparisons to determine differences between HIIT and MICT. Sex-based subgroup analyses will also be performed for exploratory purposes.

Participant data will be analyzed based on intention-to-treat; therefore, linear mixed models will be the preferred method of analysis as it is more flexible than the analysis of variance, and allows for the correlation of repeated measures within subjects and missing data, as long as missing data are missing at random [85]. Interactions between changes between primary and secondary outcomes will be explored with the Freedman-Schatzkin test, which allows for the identification of mediators of change in small-scale exercise studies [86].

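### Ending participation for randomised people who take up other structured exercise probably costs their T1 outcome, which sits badly with intention-to-treat; the rule should be confined to training

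*Protocol article*

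**What the plan says.** Under Adherence and modification to interventions, the protocol article sets three rules.

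- **Other exercise during the intervention.** "Participants will be asked to not participate in another structured exercise regimen or intervention over the course of their participation" in the HIIT or MICT group; "otherwise, they will not be allowed to continue participation".
- **Wish to stop, ill health or injury.** Where a participant wants to stop, or has a condition or injury that would "preclude safe participation of exercise over the course of the intervention, we will discontinue training".
- **Other exercise after the intervention.** "during the period between T1 and T2, participants will not be asked to refrain from further participation in exercise". Activity is instead measured with the PASIPD midway through this period.

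The Randomization section reveals allocation only after consent and T0, so the first rule acts on people already randomised.

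The Statistical analysis section says "Participant data will be analyzed based on intention-to-treat". It prefers linear mixed models because they tolerate "missing data, as long as missing data are missing at random". On timing, "The primary analysis focuses on T1, but T2 will also be included in the model".

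**The concern.** Intention-to-treat needs the outcome of everyone randomised, whatever they did afterwards. A rule that ends participation because of something a participant does after randomisation, before the primary time point, works against that. Someone removed in this way may have only T0 recorded and then adds nothing directly to the T1 contrast.

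Taking up other exercise is unlikely to be unrelated to outcome. It may reflect fitness, motivation or perceived progress. The Recruitment strategy section expects one site to draw people with a strong interest in exercise, so the behaviour is plausible here. The article names baseline score, age and sex as covariates, and those only for sub-analysis. Activity and motivation are measured at T0 but are not named as covariates. If removal depends on what the T1 value would have been, beyond what the model holds, missing at random fails. The retained arms are then selected groups under an intention-to-treat label.

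**Working it through.** **1. Does the rule end training, or study participation?** The article does not settle this, so the passages have to be compared.

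| Text | Points to |
|---|---|
| The rule speaks of participation, while the sentence before it, on stopping for other reasons, speaks of discontinuing training | leaving the study |
| No section says that people removed under the rule attend T1 or T2 | leaving the study |
| The retention telephone calls cover only T1 to T2 | no provision for those removed before T1 |
| The rule ties participation to the HIIT or MICT group, in a section on interventions | training only |
| The Assessments section has all outcomes except enjoyment collected from T0 to T2 | training only, if applied to everyone randomised |

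The change of wording between adjacent sentences, together with the silence on follow-up, makes leaving the study the natural reading. It remains an inference.

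**2. The plan's own figure.** The Sample size estimation section gives 32 per group, 80% power, alpha 0.05 and 20% attrition. 32 / (1 − 0.20) = 40 per group, which matches the stated 80 in total. The allowance is 0.20 × 40 = 8 people per arm.

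**3. A scale for the bias.** No SD is given, so the base of 32 cannot be rebuilt. Assuming a two-sided, two-sample t-test, 32 per group at 80% power implies a standardised effect of 0.71. This serves only as a yardstick.

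**4. Bias under assumed removal.** Let a share *r* of an arm be removed, and let those removed differ from those retained by *D* SD at T1 after allowing for what the model holds. The retained mean departs from the full arm mean by −*rD*. The bias in HIIT minus MICT is therefore

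bias = *r*(MICT) × *D*(MICT) − *r*(HIIT) × *D*(HIIT).

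All values of *r* and *D* below are assumptions; the article gives none.

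| HIIT removed | MICT removed | *D* | Bias (SD) | Share of 0.71 |
|---|---|---|---|---|
| 5% | 15% | 0.5 in both | 0.15×0.5 − 0.05×0.5 = 0.05 | 7% |
| 5% | 15% | 1.0 in both | 0.15×1.0 − 0.05×1.0 = 0.10 | 14% |
| 10% | 10% | 0 in HIIT, 0.5 in MICT | 0.10×0.5 − 0 = 0.05 | 7% |
| 10% | 10% | 0 in HIIT, 1.0 in MICT | 0.10×1.0 − 0 = 0.10 | 14% |
| 10% | 10% | equal in both | 0 | 0% |

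Of 40 per arm, 5% is 2 people and 15% is 6. The direction depends on which arm loses more people and on the sign of *D*; neither is known.

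**5. Power.** Removals that stay within the 20% allowance leave at least 32 per arm and power of at least 80%. If they come on top of it, and the effect is 0.71 SD:

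| Total loss | Per arm | Power (t-test) |
|---|---|---|
| 20% | 32 | 80% |
| 25% | 30 | 77% |
| 30% | 28 | 74% |
| 35% | 26 | 71% |

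**The case against.** The strongest reply is that participation here means the training programme. The sentence names the HIIT or MICT group, the section concerns interventions, and the Statistical analysis section promises intention-to-treat. On that reading training stops, assessment continues and there is no conflict. A fuller protocol, not shown, may say so. This stands as far as it goes: the article does not state that T1 and T2 are forgone, and a reader who takes that as fact, or sees a proven contradiction with intention-to-treat, goes beyond the text. Nor does the article say that data already collected are deleted or that anyone is excluded from the analysis. But a site following the sentence as written could reasonably withdraw the participant, and a different verb is used one sentence earlier. The wording needs correcting on either reading.

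Other inferences that a reader might draw are too strong.

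- **Different uptake by arm breaks missing at random.** Arm alone does not, because arm is in the model. Dependence on the unseen outcome, given the modelled variables, is what matters. That is plausible here but not shown.
- **A bias well above 0.10 SD.** Removing 20% of one arm and none of the other at *D* = 1 would give 0.20 SD, but it would use that arm's whole attrition allowance on this one cause. The Exclusion criteria already bar people in a structured programme, and participants train three times a week.
- **Removals necessarily cost power.** They do so only beyond the planned 20%.
- **The same fault affects people who stop training for other reasons.** The text there only discontinues training; it does not remove them from the study.

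**Conclusion.** The point holds in a limited form. The article states a post-randomisation rule, acting before the primary time point, that on its natural reading ends study participation because of participant behaviour, and it provides no follow-up for those affected. That is a poor fit with intention-to-treat and with a model that is valid only "as long as missing data are missing at random". If training alone was meant, the sentence does not say so.

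The size cannot be fixed from the document. Under the assumed differential removal the bias is 0.05 to 0.10 SD, about 7% to 14% of a design effect that is itself back-solved from an assumed two-sided t-test. It is zero when removal and difference are equal across arms. The sample size needs no change. The case rests on the mismatch between the rule and the analysis principle, not on these figures. The change is worth making because it is cheap and removes an avoidable source of selection.

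**What to change.** Rewrite the sentence so that stopping the assigned training and leaving the study are separate events. Whether outside exercise should end training is a clinical rule and is not judged here. Whatever that rule is, state that every randomised participant is invited to T1 and T2 on schedule unless they withdraw consent to assessment, that outside exercise is recorded, and that the participant is analysed in the arm to which they were randomised.

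No new instrument is needed. The PASIPD is already collected at all time points, and the T1 to T2 rule already allows outside exercise and measures it. The Trial status section shows recruitment still under way, so the change could apply to later participants.

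The cost is one changed sentence, a few assessment visits for people who would otherwise have left, and possibly a slight dilution of the contrast if the outside exercise affects the outcome. That dilution belongs in an intention-to-treat estimate.
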